### Randomisation and double-blind

Allocation will follow a computer-generated block randomisation list compiled by a biostatistician. The randomisation drug numbers will be sealed in opaque envelopes. All envelopes will be filed with the corresponding CRFs after use. Researchers and patients will not be informed about the specific randomisation. To ensure concealment of allocation, a study designer who is not involved in the trial implementation and data analysis is responsible for the randomisation list. Unblinding and data analysis will be started after all the participants finish the follow-up.

### Bias control

The inclusion and exclusion criteria of this study are clearly designed to reduce selection bias. Detailed data collection and strict quality management procedures will be formulated. All procedures are in accordance with the unified standard operating procedure (SOP), and trial-related tests will be conducted by experts at West China Hospital of Sichuan University to ensure the consistency of the results and reduce information bias. The final outcomes will be analysed by comprehensive statistical methods such as standardization, multivariate analysis, and propensity scoring to control for confounding factors.

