### Study design and intervention

NINCFB is a prospective, multicentre, double-blind, randomised, parallel, placebo-controlled trial studying NCFB in Chengdu city, Sichuan Province of China (Fig. 1). It is recruiting 119 patients with NCFB from 6 hospitals located in Chendu city and randomly (2:1) assigning these patients into an N-acetylcysteine (NAC) group (*n* = 79) and a control group (*n* = 40). Participants in the NAC group will be given oral N-acetylcysteine (produced by Hainan Zambon Pharmaceutical Co., Ltd.; national medicine permission number: H20000471; 600 mg, twice daily) for 52 weeks, while the control group will receive oral placebo (produced by Hainan Zambon Pharmaceutical Co., Ltd.; 00520C0; 600 mg, twice daily) for 52 weeks. All the participants will be followed up throughout the intervention period and will be required to provide relevant information about their demography, aetiology, symptomatology, bacteriology and radiography. The results will be analysed and presented in other papers. Study enrolment started on 3 March 2021 and is expected to be completed on 31 December 2024.

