### Statistical analysis

The resulting data will then be analysed with SPSS V.26 by statistical experts. Primary outcomes of each group will be compared by Student’s t test (t test) or the Wilcoxon rank-sum test after calculating its normal distribution and will be expressed in terms of the mean, standard deviation (SD) or median to indicate the long-term efficacy of NAC for NCFB. The comparison between the NAC group and the control group in terms of 16S rRNA and the levels of inflammatory factors and oxidative stressors will be of vital importance. In addition, NINCFB will also use the t-test, chi-square test and Wilcoxon rank-sum test to evaluate baseline discrepancy and other variables. Regression analysis and the correlation coefficient may confirm the predictors of disease progression and indicators of NAC efficacy.

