### Sample size

We calculate the sample size required for the evaluation of primary outcome-1 (SGRQ scores) and primary outcome-2 (number of exacerbations) respectively. As NAC is effective in reducing sputum of patients with NCFB in clinical practice, we design a ratio of 2:1 for the sample size of intervention group to control group in this study so that two-thirds of enrolled patients could receive effective treatments. For the SGRQ score, we regard mean difference (MD) of 6 points of SGRQ score as the smallest clinically important difference between two group with a standard deviation (SD) of 8.5 used in the calculation, according to the previous report of NAC on patients with COPD [35–37]. Based on 90% power with a two-sided significance level of 5%, a sample size of 64 for intervention group and 32 for control group is needed as calculated by the software PASS 15. In addition, assuming 20% of patients in each group may drop out or lose data integrity, we need to recruit 79 in the intervention group and 40 in the control group. For the number of exacerbation, we regard MD of 0.7 times of exacerbation per year as the smallest clinically important difference between two group with a SD of 1 used in calculation, according to the published study of NAC on patients with postinfection or idiopathic bronchiectasis [21]. Considering 20% dropout, we also need to recruit 79 patients in NAC group and 40 patients in placebo group (α = 0.05, 1 - β = 0.9). Taken together, this study eventually aims to enroll 119 participants, of them, 79 in the NAC group and 40 in the placebo group.

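### The unadjusted primary test in Statistical analysis is not reconciled with the open list of confounding adjustments in Bias control

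*Protocol article*

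**What the plan says.** Statistical analysis assigns the primary outcomes to a two-group test: "Primary outcomes of each group will be compared by Student’s t test (t test) or the Wilcoxon rank-sum test after calculating its normal distribution". It mentions no covariates for that comparison. The same section plans tests at baseline: "NINCFB will also use the t-test, chi-square test and Wilcoxon rank-sum test to evaluate baseline discrepancy and other variables".

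Bias control then turns to the final outcomes, for which it plans methods "such as standardization, multivariate analysis, and propensity scoring to control for confounding factors". The list is open, the covariates are not named, and final outcomes is not defined.

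The design is a "prospective, multicentre, double-blind, randomised, parallel, placebo-controlled trial". On allocation, Randomisation and double-blind says: "Allocation will follow a computer-generated block randomisation list compiled by a biostatistician". That section adds that someone outside trial conduct and analysis holds the list, so that allocation stays concealed. On timing it says: "Unblinding and data analysis will be started after all the participants finish the follow-up".

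Sample size works from a mean difference and an SD for each primary endpoint, at 2:1, with no term for covariate adjustment.

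**The concern.** A reader cannot tell which analysis decides whether N-acetylcysteine works. One section names an unadjusted test. Another says, without qualification, that outcomes will be analysed by a set of adjusted methods. Neither section refers to the other, and nothing ranks them.

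The reason given for adjusting is also out of place. Propensity scores and standardization for confounding address treatment that was chosen according to patient characteristics. Here a concealed random list assigns treatment, so any baseline difference between arms is due to chance. Adjusting for a strong prognostic variable is still useful, but the reason is precision, and the variable should be fixed beforehand.

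With several candidate analyses and no stated primary one, the reported p value need not come from a single planned test, and its nominal 5% level is then not assured.

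**Working it through.** **1. The sample size belongs to the unadjusted test.** Inputs from Sample size: SGRQ difference 6, SD 8.5; exacerbation difference 0.7, SD 1; two-sided 5%, power 90%, ratio 2:1, dropout 20%.

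Formula for the control arm at 2:1: n = (1 + 1/2) × (1.960 + 1.282)² × (SD/difference)², where the squared sum is 10.507.

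- SGRQ: 1.5 × 10.507 × (8.5/6)² = 31.6, so 32 control and 64 active. This is the stated 32 and 64. Power at 64:32 is 90.3% by the normal approximation and 89.7% by the noncentral t.
- Exacerbations: 1.5 × 10.507 × (1/0.7)² = 32.2, so 33 and 66. Power at 64:32 is 89.9% by the normal approximation.
- Dropout: 32/0.8 = 40. For the active arm, 64/0.8 = 80 and 63/0.8 = 78.75, which rounds up to 79. The stated 79 + 40 = 119 is reproduced within one patient.

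The stated figures thus follow from an unadjusted comparison of two means. Nothing in them corresponds to the methods in Bias control.

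**2. The sections side by side.**

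| Point | Statistical analysis | Bias control |
|---|---|---|
| Which outcomes | Primary outcomes | Final outcomes, undefined |
| Method | t test or Wilcoxon | Standardization, multivariate analysis, propensity scoring; list left open |
| Covariates | None for the primary comparison | Not named |
| Status | Stated comparison for the primary outcomes | Not stated |

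No sentence elsewhere in the article ranks the two columns.

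**3. Illustration of what an unranked choice could cost.** The documents give no baseline–outcome correlation, so 0.3, 0.5 and 0.7 are assumed. Trials were simulated with no treatment effect, 64 against 32 patients and a continuous outcome, 4,000 per setting. One covariate had the assumed correlation with the outcome, and four weaker covariates had 0.15 each. Each trial was analysed by a t test, by ANCOVA on the first covariate, and by ANCOVA on all five.

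| Assumed correlation | t test alone | Smallest p of the three |
|---|---|---|
| 0.3 | 5.3% | 7.7% |
| 0.5 | 5.4% | 9.2% |
| 0.7 | 5.4% | 10.2% |

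The Monte Carlo standard error is about 0.3 points near 5% and 0.5 points near 10%. A repeat with another seed and 6,000 trials per setting gave 7.9%, 8.9% and 9.8% for the last column. Each analysis alone holds about 5%; the excess comes only from choosing among them.

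**4. What fixing one adjusted model would do.** If 8.5 is the SD of the raw SGRQ score, which the article does not make clear, ANCOVA on baseline SGRQ leaves a residual SD of 8.5 × √(1 − r²). That is 8.11 at r = 0.3 and 6.07 at r = 0.7. Power at 64:32 for a 6-point difference rises from about 90% to 92.3% and 99.5%. If 8.5 already describes change scores, this gain does not follow.

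**The case against.** The best defence is that the sections need not conflict. Statistical analysis speaks of primary outcomes; Bias control is a general paragraph, uses an undefined term and never says primary. Its methods could be supportive, or could serve the search for predictors of progression, where confounding is real. An analysis plan that is not shown could rank the analyses and fix the covariates. This stands as far as it goes: the text supports unreconciled, not contradictory. It does not remove the point, because the article states without qualification how the final outcomes will be analysed and gives a reason that does not suit a randomised comparison.

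Four stronger readings are tempting but lack support in the document:

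- **Baseline tests trigger the adjustment.** The tests are planned, but no sentence links them to any adjustment.
- **The headline result will be chosen after unblinding.** The article says when unblinding and analysis start, not when methods are chosen.
- **Propensity scoring will cost power.** Matching 32 controls 1:1 would leave 32:32 and about 79% power for either endpoint, but matching is never mentioned. Weighting or covariate adjustment keeps every patient.
- **Bias control alone roughly doubles the type I error.** Taking the smallest p of a raw t test, a Wilcoxon test and a t test on change scores already gives about 9% to 10%, without any method from that section. Large figures for a wider menu therefore mostly measure something else.

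Adjusted analysis with covariates fixed in advance is not an error.

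**Conclusion.** The point holds as an unreconciled statement of the primary analysis, joined to a confounding rationale that does not fit concealed random allocation. It should be corrected, but it does not undermine the design: the sample size reproduces, and a single planned analysis holds its level.

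The size is illustrative. A type I error of about 8% to 10% instead of 5% rests on assumed correlations of 0.3 to 0.7, a normally distributed outcome, assumed covariates, and selection of the smallest p among three analyses. The document announces no such selection. No figure was derived for the exacerbation count.

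**What to change.** Before unblinding:

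1. Name one primary model per endpoint, with covariates fixed in advance: baseline SGRQ for the SGRQ endpoint, and exacerbations in the year before enrolment for the exacerbation endpoint. Table 2 already collects both at baseline.
2. Remove standardization and propensity scoring from the randomised comparison in Bias control, or label any adjustment beyond the primary model as a sensitivity analysis with its covariates listed. Confounding control for the predictor and biomarker analyses can stay, if the text says that is its purpose.
3. Describe baseline characteristics by arm, and do not use significance tests to choose covariates.

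The target of 119 is unchanged and no new data are needed. The cost is a documented, dated amendment to the stated primary test while the trial is under way. If the sponsor prefers to keep the unadjusted test as primary, labelling the Bias control methods as supportive would resolve the inconsistency, but would forgo the likely gain in precision.

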### Dissemination plans

The results will be published in high-quality peerreviewed journals at the end of study.

## Discussion

NINCFB is being conducted to reveal the long-term efficacy of NAC in QoL and exacerbations of patients with NCFB and to explore the influence of NAC on airway bacterial colonization, chronic inflammation, oxidative stress and other manifestations.

Although NCFB is receiving increasing attention from patients and clinicians, there are a few relevant trials on its evaluation, management and treatment [1, 9]. According to investigations on Web of Science, nearly 520 articles of NCFB were published between 2012 and 2022, but less than 25 of them are randomised controlled clinical trials (RCTs) [1]. More high-quality evidence needs to be established for diagnosis and management of NCFB. This study is a multicentre, double-blind, randomised, placebo-controlled trial designed to provide new evidence for NCFB therapy and supervision.

Low QoL and repeated exacerbations cause distress in patients with NCFB and greatly increase their economic burden, and these would be the primary problems we should solve. Bacterial infection and airway bacterial colonization are considered the main causes of exacerbations of bronchiectasis not due to cystic fibrosis [38]. However, drug resistance and difficulty in eradicating biofilms with systemic antibiotics have led physicians to consider the possible role of nonantibiotic therapy [17].

Accordantly, the usage of expectorant might help to relive the continual expectoration and thus improve the life quality and reduce exacerbations in patients with NCFB, however, the relevant RCTs with comprehensive efficacy evaluation are limited (Table 4). Among the reported expectorants, the usage of inhaled mannitol and nebulised hypertonic saline showed no substantial improvement effects on the SGRQ score and exacerbations of patients with NCFB. By contrast, given the pharmacological action of NAC in antibiosis [17], researchers in Shandong Province of China have designed and conducted a relatively long-term (12 months) randomised controlled trial to demonstrate that NAC decreased the number of exacerbations in patients with NCFB [21]. However, they only included the patients with postinfection and idiopathic bronchiectasis, but not patients caused by immune deficiency and congenital defects, who also take NAC regularly to clear airway mucus in clinical practice; In addition, this study did not investigate the long-term performance of NAC in antibiosis, anti-inflammation and antioxidation; Furthermore, the therapeutic discrepancy of NAC among patients with different pathogenic (other than postinfection and idiopathic bronchiectasis), airway bacterial colonization, QoL scores, lung functions and exacerbation/hospitalization frequency were not assessed. As there is no expectorant proven to exert long-term efficacy against NCFB, a clinical trial to investigate the long-term therapeutic effects of NAC on the patients with NCFB is urgently needed. Consequently, to provide more comprehensive and stronger evidence for the benefits of NAC, our trial will not only evaluate the long-term efficacy of NAC on QoL and exacerbations of patients with NCFB, but also determine its effects on the pulmonary microbiology, inflammation, oxidative stress and identify the discrepancies of NAC efficacy related to disease heterogeneity.

**Table 4 Tab4:** Previous RCTs reporting the effects of expectorant on NCFB patients

Study	Expecto-rants	Groups	Participants	Findings
Bilton et al. 2013 [39]	Mannitol	^a^E: inhaled mannitol 320 mg, twice a day for 12 weeks (*n* = 231) ^a^C: inhaled placebo 320 mg, twice a day for 12 weeks (*n* = 112)	1) 15–80 years of age 2) Clinically stable (for ≥2 weeks prior to study entry) and persistent cough 3) Chronic sputum (> 10 mL/d on the majority of days in the 3 months prior to enrollment) 4) Chronic chest congestion (chronic excessive accumulation of mucus) 5) FEV_1_ > 50% predicted 6) Having no active signs of asthma, malignancy, or TB, or uncontrolled hypertension, or smoking history.	There was no statistical difference between the groups in total SGRQ score. The changes in sputum weight over 12 weeks between mannitol and placebo group had significant difference, which appeared to be associated with increased antibiotic use in the placebo group.
Bilton et al. 2014 [40].	Mannitol	E: inhaled mannitol 400 mg, twice a day for 52 weeks (*n* = 233) C: inhaled mannitol 50 mg, twice a day for 52 weeks (*n* = 228)	1) 18–85 years of age; 2) Having at least two exacerbations in the previous 12 months; 3) Having a minimum SGRQ score of 30; 4) Producing at least 10 g of sputum a day; 5) FEV_1_ ≥ 40% and ≤ 85% predicted; 6) Having no mannitol-induced bronchospasm.	The decreasing in total SGRQ score over the treatment period in E group was more obvious than C group, while the changes in annual exacerbation rate, sputum weight, FEV_1_, and FVC between the two groups had no difference.
Kellett et al. 2011 [41].	Hypertonic saline	E: nebulised 7% hypertonic saline 4 mL, once daily for 12 weeks (*n* = 28) C: nebulised 0.9% sodium chloride 4 mL, once daily for 12 weeks (n = 28)	1) ≥ 18 years of age; 2) Having no bronchoconstrictor response to 7% hypertonic saline.	The changes in SGRQ score between the groups had no significant difference, while FEV_1_ and FVC during experimental phases had improved.
Nicolson et al. 2012 [42].	Hypertonic saline	E: nebulised 6% hypertonic saline 5 mL, once daily for 48 weeks (*n* = 20) C: nebulised 0.9% sodium chloride 5 mL, once daily for 48 weeks (n = 20)	1) ≥ 18 years of age; 2) Clinically stable; 3) Producing sputum daily 4) Reported ≥2 exacerbations requiring antibiotics per year for the previous 2 years. 5) FEV_1_ decreased by less than 15% after the hypertonic saline challenge and their FEV_1_ was more than 1 L at baseline.	The changes in SGRQ score, exacerbation rate, FEV_1_, and FVC between the two groups during 48 weeks had no difference.
Qi et al. 2019 [21]	NAC	E: NAC 600 mg, twice a day for 48 weeks (*n* = 81) C: as-needed therapy for 48 weeks (*n* = 80)	1) Diagnosis of idiopathic or post-infective bronchiectasis; 2) 18–80 years of age; 3) Clinically stable; 4) ≥ 2 exacerbations in the past year; 5) Having no cigarette smoking within 6 months; 6) FEV_1_ > 30% predicted 7) Having no active signs of asthma or malignancy.	The exacerbation frequency over the treatment period and 24-h sputum in E group was lower than C group. FEV_1_ and FVC between the two groups had no difference.

*TB* tuberculosis

^a^“E” means experimental group while “C” means control group

## Data Availability

The corresponding results will be published in high-quality journals after analysis. The raw datasets used and analysed during the current study will be available from the corresponding author on reasonable request.

## Abbreviations

NCFB: Non-cystic fibrosis bronchiectasis
NAC: N-acetylcysteine
QoL: Quality of life
COPD: Chronic obstructive pulmonary disease
ABPA: Allergic bronchopulmonary aspergillosis
NTM: Active nontuberculous mycobacterium
SGRQ: St George’s Respiratory Questionnaire
BSI: Bronchiectasis severity index
mMRC: Modified British Medical Research Council
HRCT: High-resolution computed tomography
FEV1: Forced expiratory volume in 1 s
CRF: Case report form
IL: Interleukin
TNF: Tumour necrosis factor
MMP: Matrix metalloproteinase
MPO: Myeloperoxidase
TAC: Total antioxidant capacity
SOD: Superoxide dismutase
MDA: Malondialdehyde
